## Methods

### Study design and recruitment

This protocol is presented in accordance with the SPIRIT Initiative 2013 (Additional file 1), an evidence-based guide for the content of trial protocols. This study is a single-center, parallel, randomized, sham-controlled trial in which patients and assessors will be blinded. Patients with CKD undergoing HD will be recruited at Instituto do Rim by invitation after the benefits of tDCS for chronic pain syndromes is explained to them. To help achieve adequate participant enrolment, flyers will be placed at the recruitment site and physicians will be informed of the study to assist with identifying potentially eligible participants.

This study will be conducted at the Federal University of Rio Grande do Norte, Natal, Brazil and registered with the Brazilian Clinical Trials Registry ReBec (www.ensaiosclinicos.gov.br/rg/RBR-7qk2cs/), registration number U1111–1216-0137; June 20, 2018. Data will be stored at Motricity Lab—Federal University of Rio Grande do Norte and will be archived with the principal investigator for 5 years and then destroyed. Possible changes to the protocol will be communicated to the local Ethics Committee, ReBec, and participants. Documents will not be made public without the permission of the participants and resulting publications will not identify the subjects.

All participants will be informed about the trial’s objectives and procedures and that participation is voluntary, as determined by resolution No. 466/12 of the National Health Council. Potentially eligible patients with CKD undergoing HD who are willing to know more about the study will receive a detailed study explanation from the study research coordinator, including objectives, procedures, risks, and benefits of the study and all questions will be answered. Interested patients will be asked to sign an informed consent form (Additional file 2) before entry into the study. Informed consent will be obtained by the research team before study assessments and study procedures are performed and before any private information is recorded. After agreeing to participate in the trial, all participants will sign the informed consent form, which was submitted and approved by the ethics committee of the Faculty of Health Sciences of Trairí—Federal University of Rio Grande do Norte (number 2.678.737). Adult patients assisted in the dialysis center will be recruited.

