### Randomization method

Eligible and consenting patients will be randomized using the order of entry into the study and a previous computer-generated randomization list, using random blocks of six patients (for each six patients, two will be randomized to each group) to minimize the risk of unbalanced group sizes. A research assistant external to the study will generate the allocation sequence. Each participant will be equally likely to belong to any one of the groups. Opaque envelopes will be used to conceal allocations. Participants and researchers involved in the assessments and interventions will be blind to group allocation throughout the trial.

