### Blinding

Patients and evaluating researchers will be blinded. To ensure patient blinding, the electrodes of the sham group will be placed in the same position as for active groups. The anodal electrode will be placed over the motor cortex and the cathodal over the contralateral supraorbital area, according to placement procedures described below. Usually when the current initiates, patients report itching or a tingling sensation under the electrodes for 2 or 3 minutes. This method of sham intervention is therefore designed to provide an initial period of tingling so that similar sensations are perceived as during active tDCS [11]. For the placebo group a ramp-up of 30 s and a ramp-down of 30 s will be used. The device displays are identical in active and sham settings. To ensure the success of blinding, we will ask participants and outcome assessors at the endpoint to guess whether the treatment was active or sham. Researchers involved in the assessments will be blinded to group allocation throughout the trial.

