### Intervention

A total of ten sessions lasting 20 min each will be administered to participants over Monday/Wednesday/Friday or Tuesday/Thursday/Saturday (three sessions per week) by a trained physician at the Instituto do Rim (Fig. 1). The tDCS method will use a monophasic continuous current with an intensity of 2 mA for 20 min (Fig. 2). Each patient will be awake and sit in a comfortable chair with back and arm support during the tDCS intervention. tDCS will be performed before the usual session of dialysis.

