**Fig. 2 Fig2:**
[figure not shown]
Illustration of electrode replacement. **a** M1 group. The anodal electrode will be placed over the motor cortex and the cathode over the supra-orbital contralateral area (C3/Fp2 montage). **b** DLPFC group. The anodal electrode will be placed over the DLPFC and the cathode over the supra-orbital contralateral area (F3/Fp2 montage). Electrodes will the placed according to 10/20 EEG international system. Electrode size 35 cm^2^ with a current density of 0.057 mA/cm^2^

During the baseline period, patients will be randomized at a ratio of 1:1:1 to receive sham tDCS (sham group), active tDCS of the primary motor cortex (M1 group), or active tDCS of the left DLPFC (DLPFC group). The M1 was chosen because studies show that stimulation of this area is associated with pain improvement [9, 11, 15, 16]. The left DLPFC was chosen because several studies with neuromodulation have shown that stimulating this area is associated with improvement of depression and also induces an analgesic effect in fibromyalgia [9, 15]. The electrodes will be placed into a 35 cm^2^ square sponge immersed in saline solution (150 mMols of NaCl diluted in water Milli-Q). For stimulation, a gradual current ramp-up and ramp-down with 30-s duration will be used. Electrodes attached to the scalp will be supported by an elastic band. The electrodes (anode and cathode) will be connected to a battery-powered (9 v) stimulator with current verified by a precision digital multimeter (DT832, WeiHua Electronic Co., Ltd, China) with standard error of ±1.5%.

For ethical reasons, no changes will be made to HD routines (days and the place of sessions), clinical care (medicines, imaging, or blood exams), and previous prescription of painkillers or other medication.

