### Adverse event monitoring and adherence

To date, the use of conventional tDCS protocols in human trials (20 min, 2 mA, and ten sessions, in the case of this trial) has not produced any reports of serious adverse effects or irreversible injury [24]. Adverse events will be carefully monitored during all steps of the study by asking patients, after each session of stimulation and during the follow-up period, whether they had experienced any adverse events, and the relationship of these events to treatment with tDCS. The most commonly reported minor adverse events include the sensation of tingling or discomfort under the electrode sites, reported in both active and sham conditions [24, 25]. These events include participant ratings of frequency, severity, importance, and associated distress. To evaluate the adverse effects, we will record any musculoskeletal symptoms such as pain and fatigue, itching, tingling, headache, burning, discomfort, or cardiovascular symptoms such as shortness of breath, chest pain, and abnormal increase in blood pressure. Participants will receive care as appropriate for any harm that arises as a result of study participation.

A doctor will be on duty during tDCS sessions to handle any adverse events, including problems with dialysis. The researchers will communicate any important protocol modifications to relevant parties.

The main strategy to improve adherence of patients is to perform tDCS during HD sessions and explain to participants the relevant contribution to the treatment of chronic pain, including the possibility of improving pain. There will also be flexible hours offered for receiving therapy according to the HD, as well as direct contact by telephone with participants confirming the evaluation dates and reinforcing treatment adherence.

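### The plan says staff who deliver the interventions are blind to group, but electrode position shows the DLPFC arm to whoever places the electrodes

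*Protocol article*

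**What the plan says.** Three places in the protocol article describe who is blind.

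- Randomization method: "Participants and researchers involved in the assessments and interventions will be blind to group allocation throughout the trial".
- Study design and recruitment: a "sham-controlled trial in which patients and assessors will be blinded".
- Blinding: "Patients and evaluating researchers will be blinded". The closing sentence of that section returns to researchers who carry out assessments and does not mention those who deliver treatment. The end-of-trial guess of active or sham is asked of participants and outcome assessors only.

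On delivery, the Intervention section says "A total of ten sessions lasting 20 min each will be administered to participants", given "by a trained physician at the Instituto do Rim". The Fig. 2 caption gives the M1 montage: "The anodal electrode will be placed over the motor cortex and the cathode over the supra-orbital contralateral area (C3/Fp2 montage"). For DLPFC it gives F3/Fp2.

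On sham, the Blinding section first says that the electrodes sit where those of the active groups (plural) sit. It then gives one position, with the anode over the motor cortex and the cathode over the opposite supraorbital area. It adds that the device shows the same display in active and sham settings. The Intervention text after Fig. 2 describes a battery-powered "stimulator with current verified by a precision digital multimeter".

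**The concern.** The Randomization method sentence is the only text that extends the blind to those who give the stimulation. The other two statements leave that role out, and the blinding check does not test it. The claim also sits badly with the procedures: the two active arms use different scalp positions, and whoever places the electrodes has to know which one to use.

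The stake is performance bias. Pain VAS, MPQ and BDI are reported by the patient, and the operator sees each patient ten times. An operator who knows the arm could convey expectation without meaning to. If the final report repeats the sentence as it stands, readers will credit the trial with a safeguard that its design does not have.

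**Working it through.** There is no sample size, power or alpha figure to reproduce here. The check sets the statements side by side and counts what electrode position reveals.

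**Inputs**
- 45 patients, three groups of 15 (Sample size).
- Ten sessions per patient (Intervention).
- M1 anode at C3, DLPFC anode at F3 (Fig. 2 caption).
- Sham anode over the motor cortex, by the specific sentence in Blinding; or at the positions of the active groups, by the general sentence there.

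Total sessions if all 45 patients complete treatment: 45 × 10 = 450.

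**Reading A: all sham patients at the motor cortex**

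| Position seen | M1 | DLPFC | Sham |
|---|---|---|---|
| C3 | 15 | 0 | 15 |
| F3 | 0 | 15 | 0 |

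- At F3 the arm is certain: 15 of 45 patients, and 15 × 10 = 150 of 450 sessions.
- At C3 there are 30 patients, and position leaves M1 and sham equally likely (15 against 15).
- Best-guess accuracy for the arm, from position alone: (15 + 15)/45 = 30/45 = 66.7%. Chance is 1/3 = 33.3%.

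**Reading B: sham split equally over the two sites** (an assumption; the document states no split)

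| Position seen | M1 | DLPFC | Sham (average) |
|---|---|---|---|
| C3 | 15 | 0 | 7.5 |
| F3 | 0 | 15 | 7.5 |

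- No patient's arm is certain, but position rules out one active arm for all 45 patients.
- Best-guess accuracy: (15 + 15)/45 = 66.7% again.

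**What this settles.** Under either reading, the person placing the electrodes is not blind to group. Under Reading A, which follows the only explicit sham position in the text, the whole DLPFC arm is open to that person at every session.

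**What it does not settle.** Under Reading A, M1 and sham share a montage and the displays are identical, so position says nothing about that contrast. The multimeter could show a difference if it were read after the sham ramp-down, but the article does not say who reads it or when.

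**The case against.** The best defence has four parts.

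First, the Study design and Blinding sections do not say that only patients and assessors are blind. They list two roles, and the Randomization method section adds a third. That is fair, and silence alone would be a weak contradiction. But the montages make the added claim untenable whatever the other sections say.

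Second, a reader might infer that the operator knows the arm of every patient, so that all three arms and all 450 sessions are affected. The document does not support this. It does not say that the operator opens the envelope, selects the setting or is told the allocation. M1 and sham share the motor-cortex position and the same display. The multimeter appears as a piece of equipment, with no stated reader or time of use. M1 versus sham could be operator-blind if the setting were preset or coded, and an article need not describe such coding. This part of the defence stands.

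Third, a reader might infer that an unblinded operator judges adverse events. The Adverse event monitoring section says that patients are asked about events and "the relationship of these events to treatment with tDCS", with participant ratings of severity and distress. It does not give the task to the operator. The message that pain may improve is an adherence message to participants generally, tied to no arm. This part stands too, so keeping the operator away from adverse-event recording is a precaution and not the correction of a stated fault.

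Fourth, all evaluations are made by a blinded physical therapist. That protects the assessor's ratings. It does not remove what an operator may have conveyed to a patient who then rates their own pain.

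**Conclusion.** The point holds in a limited form: the plan claims a blind for intervention staff that its own montages rule out. Under the explicit motor-cortex sham position, the person placing electrodes identifies every DLPFC patient, 15 of 45, in 150 of 450 sessions. If sham is split over both sites, no arm is certain but one active arm is excluded for every patient. The counts assume full recruitment, equal groups and ten completed sessions each; Reading B also assumes an equal split.

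M1 versus sham remains undetermined. The comparisons most clearly exposed are DLPFC versus sham and DLPFC versus M1. The number of sessions measures opportunity; it does not measure how far the results would be biased. The blind of patients and assessors is stated consistently, so the design stands. The claim about intervention staff should be corrected before it is carried into a report.

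**What to change.** 1. Reconcile the blinding statements in Study design and recruitment, Randomization method and Blinding. Either remove the reference to interventions from the Randomization method sentence, or say that the operator is not blind to stimulation site and is blind at most to active versus sham at C3, and state the mechanism.
2. Resolve the general sentence on sham position (as in the active groups) against the single motor-cortex position that follows it.
3. Keep the operator out of outcome assessment and out of recording and attributing adverse events. The already blinded therapist or a patient-completed checklist can do this.
4. Use the same neutral wording at sessions in all arms.
5. Do any multimeter check off the patient, identically in all arms.

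The cost is protocol wording and a reallocation of tasks among existing staff, with no change to sample size or analysis. The small downside is that the stated blind becomes less favourable: patients and assessors only.

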### Blinding

Patients and evaluating researchers will be blinded. To ensure patient blinding, the electrodes of the sham group will be placed in the same position as for active groups. The anodal electrode will be placed over the motor cortex and the cathodal over the contralateral supraorbital area, according to placement procedures described below. Usually when the current initiates, patients report itching or a tingling sensation under the electrodes for 2 or 3 minutes. This method of sham intervention is therefore designed to provide an initial period of tingling so that similar sensations are perceived as during active tDCS [11]. For the placebo group a ramp-up of 30 s and a ramp-down of 30 s will be used. The device displays are identical in active and sham settings. To ensure the success of blinding, we will ask participants and outcome assessors at the endpoint to guess whether the treatment was active or sham. Researchers involved in the assessments will be blinded to group allocation throughout the trial.

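### The only sham montage named is motor cortex, so an electrode at the DLPFC site always means active stimulation, and the claim that those delivering the intervention are blind cannot hold for that arm

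*Protocol article*

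**What the plan says.** All references are to the protocol article.

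- **Blinding, general statement:** "To ensure patient blinding, the electrodes of the sham group will be placed in the same position as for active groups".
- **Blinding, next sentence:** "The anodal electrode will be placed over the motor cortex and the cathodal over the contralateral supraorbital area, according to placement procedures described below". No other sham montage is described anywhere in the article.
- **Intervention, caption to Fig. 2:** the M1 group has the anode at C3 and the cathode at Fp2. For the DLPFC group, "The anodal electrode will be placed over the DLPFC and the cathode over the supra-orbital contralateral area", which the caption labels F3/Fp2.
- **Randomization method:** "Participants and researchers involved in the assessments and interventions will be blind to group allocation throughout the trial". Allocation is in blocks of six, two patients per arm.
- **Study design and recruitment, and Blinding:** both list only patients and assessors as blinded.
- **Intervention and Outcome measures:** a physician gives the ten sessions, and a blinded physical therapist carries out the evaluations.
- **Sample size:** 45 patients, 15 per arm.

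**The concern.** A sham protects a comparison only if nothing the staff or the patient can see separates it from the active treatment. There are two active positions here and one sham position, so the general statement in the Blinding section cannot be true for the DLPFC arm. For anyone who knows the sham rule, an electrode at F3 reveals the allocation.

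The person certain to see the position is the operator, whom the Randomization method section declares blind. The VAS and MPQ (the primary endpoint) and the BDI are reported by the patient. An operator who knows that a patient is active can convey that expectation over ten sessions, and no sham patient meets an operator with the same certainty. This could favour DLPFC over sham, and the analysis could not remove it afterwards.

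**Working it through.** The article gives no figure to reproduce on this point. The check is how much electrode position says about active versus sham.

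**Inputs**

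- Arm sizes 15 / 15 / 15, total 45 (Sample size: 36 + 9 = 45; 45/3 = 15).
- Allocation 1:1:1 (Intervention); blocks of six, two per arm (Randomization method).
- Positions: M1 active at C3 and DLPFC active at F3 (Fig. 2 caption); sham over motor cortex, hence C3 (Blinding).

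**Formula**

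P(active | site) = active patients at the site / all patients at the site.

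**As written**

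| Site | Active | Sham | P(active \| site) |
|---|---|---|---|
| F3 | 15 | 0 | 15/15 = 1.00 |
| C3 | 15 | 15 | 15/30 = 0.50 |
| Overall | 30 | 15 | 30/45 = 0.67 |

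An F3 placement moves the probability of active stimulation from 0.67 to certainty. This concerns 15/45 = 33% of all patients and 15/30 = 50% of the active patients.

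Forty-five is seven blocks of six plus three (7 × 6 = 42), so the arms may end at 14 to 16. The F3 value stays at 1.00 whatever the arm sizes, because no sham patient is placed there.

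**With sham split between the two sites**

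- Even split in expectation: 15/(15 + 7.5) = 0.67 at both sites, equal to the overall value.
- Split of 8 and 7 among 15 sham patients: 15/(15 + 8) = 15/23 = 0.65 at one site and 15/(15 + 7) = 15/22 = 0.68 at the other.
- If the incomplete last block leaves active arms of 14 to 16, the extremes are 14/(14 + 8) = 0.64 and 16/(16 + 7) = 0.70.

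Position then says almost nothing about active versus sham.

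**What each role can learn under the present text**

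- *Operator:* sees the position at every session. Knowing the sham rule is enough to identify each DLPFC patient as active. This contradicts the Randomization method section.
- *Patient:* feels where the electrodes are, but is unmasked only on learning that sham uses the other site. The article does not say that patients are told.
- *Evaluating therapist:* is unmasked only on seeing or being told the placement. The article does not say that this happens.

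**The case against.** **The general statement could mean a sham already divided over both sites.** The sentence that follows it names motor cortex alone, and the Fig. 2 caption describes no sham over the DLPFC. A full protocol may say more, but the article's two sentences conflict as they stand and have to be reconciled.

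**Double-blind may mean only patients and assessors.** This is largely right. It is how Study design and recruitment and Blinding put it, and the evaluator is a different professional from the one giving the sessions. A reader might infer that blinding of the whole DLPFC arm has failed; the documents do not show that. What fails outright is the claim about intervention staff.

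**The bias is not demonstrated.** Also right. The figure of 15/15 describes what an operator can deduce. It does not measure a shift in VAS, MPQ or BDI, and neither the size nor the direction of any bias can be computed from the article. The end-of-trial guess cannot repair bias, but it could show whether knowledge reached patients or assessors.

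**A split sham does not make operators blind to group.** This stands. An operator at F3 would still know that the patient is not in the M1 arm, and an operator who sets the device mode would know active from sham in any case. The article does not say who sets the mode.

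**Sham timing.** A reader might also infer a one-minute sham from the two 30-second ramps and set it against the statement that "patients report itching or a tingling sensation under the electrodes for 2 or 3 minutes". The text does not support this. It gives ramp durations only, leaves the time at current between them unstated, and uses 30-second ramps for stimulation as well.

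**Conclusion.** The point holds in a limited form. Position-matched sham, which the Blinding section presents as the safeguard for patient blinding, does not exist for the DLPFC arm, and F3 identifies active stimulation with certainty (1.00, against 0.50 at C3 and 0.67 overall). The statement that researchers involved in the interventions are blind cannot be true for that arm, and it goes further than what two other sections claim.

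The consequence is an exposed DLPFC-versus-sham contrast, with operator expectation as a plausible but unquantified route to bias. M1 versus sham shares one position and is not affected in this way. A reader might say that one of two primary comparisons is compromised. The article does not designate such comparisons: the Statistical analysis section specifies a mixed ANOVA with a time-by-group interaction and Bonferroni-corrected post-hoc comparisons.

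The conclusion assumes that the motor-cortex sentence applies to all sham patients and that operators know the sham rule. The first is what the text says. The second is hard to avoid for staff who place the electrodes.

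**What to change.** 1. On the randomisation list, make one of the two sham slots in each block of six a C3 sham and the other an F3 sham. Pool the sham patients for analysis. P(active | site) is then about 0.65 to 0.68 at both sites with 15 per arm.
2. Rewrite the electrode-position sentences in Blinding to describe both sham montages. Align Randomization method, Blinding, and Study design and recruitment on who is blind and to what. Operators will know the stimulation site. They can be called blind to active versus sham only if someone else sets the mode.
3. Report the end-of-trial guess by arm.

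The cost is a new list and a revised sham instruction, with no extra patients or visits. The downside is small: sham becomes a pool of two no-current montages with about 7 or 8 patients each.

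If the list can no longer be changed, correct the blinding statements, keep those who place electrodes apart from those who assess, report the guesses by arm, and state the missing F3 sham as a limitation of the DLPFC comparison.
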